### Main analysis—sequential design with the CSW approach based on age at enrollment

2.5

Emulated target trials assign men into one of the two screening arms based on their screening pattern during the eligibility period, which starts when they attain the age of interest for the study (75–79 yr) for the first time and every month thereafter (eg, at age 75 yr, 75.083 yr, 75.167 yr, and so on).

Screening is ascertained within the 1st month from trial initiation, representing the eligibility and assignment period. Eligible men with at least one PSA test in this period will be assigned to the screening arm. Those with no PSA test in this window will be assigned to the control arm. Assignment ascertainment is assumed to be accurate for all participants, as the STHLM0 contains the data on PSA testing for men living in Stockholm and who were tested in Stockholm since 2007 [22]. Considering the assumptions of causal inference frameworks [19], the following three principles are assumed to be fulfilled:1.Positivity: Every man living in Stockholm within the age group of interest has a nonzero chance of deviating from the protocol at any point during the assessment period, and every eligible man is assumed to have had the opportunity to undergo a PSA test.2.Consistency: The survival outcome we observe for the men under the given screening strategy is the same as the outcome that would have occurred if we had explicitly assigned these patients to follow the same strategy (ie, their potential outcome). As such, the screening protocol is assumed to have been defined clearly and applied consistently throughout the study period in our study. Moreover, we assume that the statistical models used in the analysis (described below) are specified correctly.3.Exchangeability: There are no unmeasured confounders; all factors that influence both the screening assignment and the likelihood of deviating from the protocol have been measured. We assume based on the confounders accounted for in the study (described below) that we address the potential factors that impact the screening assignment.

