### Eligibility criteria

2.3

Men aged 75–79 yr between 2007 and 2023, with no PCa diagnosis at the time of inclusion (based on each trial emulation), will be considered eligible for the trials. To ensure proper control for potential confounding and to be able to evaluate the eligibility criteria, only men with complete information on their screening status, outcomes, and confounders in the registers will be included. The summary number of the men excluded due to missing values will be described in the final study flowchart.

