### Assignment to screening strategies

2.6

Since randomization is not possible in the emulation of target trials, men will be assigned to the screening strategy in each of the trials based on their observational data. Considering that the intention of the PSA test is not recorded in the register, additional measures will be taken to ensure proper capture of the PSA-based screening instead of diagnostic PSA testing. Men who have had an immediate diagnosis following their PSA test (ascertained as within 6 mo from the test), and the diagnosis showed distant metastasis (M1) or the diagnosis was prompted by urinary or other symptoms, the PSA test will not be classified as a PSA-based screening test. If the PSA test was preceded by urological symptoms or bone pain within 6 mo in the patient register, the test will not be classified as a PSA-based screening test. Moreover, we will not consider men as screened if they underwent a PSA test, but have no record of PCa diagnosis in the registers, yet died from PCa within 6 mo of the PSA test. We will assume that the adjustment for the confounders is sufficient to mimic the randomization in the target trial (ie, we assume that they are randomly assigned within the levels of the confounders). Considering the observational nature of the study, blinding is not possible, and the men will be aware of their screening activity.

Figure 1A illustrates the flowchart of the inclusion into the trial based on the main analysis design.

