### Follow-up period

2.7

Men will initiate their follow-up based on the time of inclusion, starting from January 1, 2007, and end their follow-up by December 31, 2023, or if they experience the outcome of interest, whichever occurs first. The last recruitment age is 79.91 yr. The date of inclusion (time zero) will depend on the trial design; in the main analysis, this will be the date of age attainment.

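### A PSA test taken after a prostate cancer diagnosis in the same month can place a known case in the screening arm

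*Protocol article*

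**What the plan says.** Four parts of the protocol article act together.

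- **Eligibility (2.3).** Men are eligible "with no PCa diagnosis at the time of inclusion (based on each trial emulation").
- **Time zero (2.7).** The date of inclusion depends on the design; "in the main analysis, this will be the date of age attainment". That is the first day of each monthly trial.
- **Assignment (2.5).** "Screening is ascertained within the 1st month from trial initiation, representing the eligibility and assignment period". Then: "Eligible men with at least one PSA test in this period will be assigned to the screening arm". Nothing is said about the order of test and diagnosis within the month.
- **Censoring (2.10.2).** A control clone is censored at the first screening date in the month. A screening clone is censored at the end of the month if no screening occurred.

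Section 2.6 narrows what counts as screening: "additional measures will be taken to ensure proper capture of the PSA-based screening instead of diagnostic PSA testing". It sets three filters:

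1. "Men who have had an immediate diagnosis following their PSA test (ascertained as within 6 mo from the test"), where the disease was metastatic or the diagnosis was prompted by symptoms.
2. "If the PSA test was preceded by urological symptoms or bone pain within 6 mo in the patient register".
3. Death from prostate cancer within 6 months of the test, with no diagnosis on record.

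**The concern.** A PSA measurement soon after diagnosis, for staging or before treatment, is not screening. If it places the man in the screening arm, that arm gains someone who certainly has prostate cancer and whose cancer the test did not detect. His control clone leaves at the same test, so his later death counts only under screening.

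Adjustment cannot remove this. The confounders in 2.10.1 do not include a prostate cancer diagnosis, and this diagnosis arises after time zero. The limitations in 3.3 mention symptom-prompted tests and rechecks after a raised value, but not tests after diagnosis.

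The direction matters. Section 2.1 expects only a modest benefit, through prostate cancer mortality. Section 3.1 says that a null or harmful result should strengthen advice against screening after 74.

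**Working it through.** **1. Follow one man through the rules.** He has no diagnosis on day 0, is diagnosed on day 10, and has his first PSA test of that month on day 20.

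| Rule | Result |
|---|---|
| 2.3 and 2.7: no cancer at time zero | Eligible |
| 2.5: a PSA test within the month | Screening arm |
| 2.6, filter 1: diagnosis after the test | Does not apply; the diagnosis came first |
| 2.6, filter 2: recorded symptoms before the test | Applies only if he had such symptoms on record |
| 2.6, filter 3: cancer death without a diagnosis | Does not apply; he has a diagnosis |
| 2.10.2: control clone | Censored on day 20 |

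Filter 1 can also be undone. Suppose a man's test in an earlier month is declassified because he proved to have metastases. A further test after diagnosis, in the month of diagnosis, is not followed by a diagnosis. Unless filter 2 catches him, he enters the screening arm of that month's trial.

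**2. The plan's own figures.** The protocol does not size this problem. Its only design calculation, Table 1, concerns all-cause mortality. It reproduces on an assumed two-sided 5% level: for HR 0.956, √(35 000 × 0.2 × 0.8) × |ln 0.956| − 1.96 = 74.83 × 0.0450 − 1.96 = 1.41, which is 92.0% power. The point here does not depend on it.

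**3. Illustrative size.** All inputs are assumptions. Let *i* be annual incidence, *q* the share of newly diagnosed men whose first test of the month comes after diagnosis, *m* the monthly probability of a PSA test, and *e* the excess risk of death in these men.

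- Share of screening-arm entries: s = (i/12 × q) / (m + i/12 × q)
- Added cumulative incidence in that arm: s × e

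*Set A:* i = 0.5–1.0%, q = 20–50%, and m = 1 − 0.80^(1/12) = 1.84%, which takes the 20% in 2.12 as an annual testing rate. The 10-year prostate cancer death risk is 15–25% in these men against 3% in others, so e = 12–22 points.
- Low: 0.0000833/(0.0184 + 0.0000833) = 0.45%; × 12 = 0.05 points.
- High: 0.000417/(0.0184 + 0.000417) = 2.2%; × 22 = 0.49 points.
- Against the assumed 3% base, that is about 2–16% in relative terms.

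*Set B:* i = 0.3–1.0%, q = 5–30%, m = 2–4%, excess long-term mortality 10–30 points.
- Low (0.3%, 5%, 4%): s = 0.03%; × 10 = 0.003 points.
- Middle (0.6%, 10%, 2%): s = 0.25%; × 10 to 30 = 0.025–0.075 points.
- High (1.0%, 30%, 2%): s = 1.2%; × 30 = 0.37 points.

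**4. Direction.** Men diagnosed before any test in the month make up at most i/12 of all entrants (0.025–0.083%), and a correct screening arm would contain them at that share. The bias is against screening whenever s exceeds i/12. It does at all four range ends above. Subtracting i/12 lowers the upper ends only slightly: (2.21 − 0.08)% × 22 = 0.47 points in set A, and (1.23 − 0.08)% × 30 = 0.35 points in set B.

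**The case against.** **The filters.** A reader might infer that every PSA test in the month counts as screening. The document does not support that: 2.6 removes three classes of test with the stated aim of excluding diagnostic ones, and its symptom filter will remove some men with a recent diagnosis. What stands is that no filter acts on a diagnosis that precedes the test.

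**When eligibility is judged.** Section 2.5 calls the month both the eligibility and the assignment period, and Figure 1 is not shown, so a check on day 0 alone is the natural reading of 2.3 and 2.7 rather than an explicit statement. The other reading does not help. Requiring men to stay free of cancer all month would drop a man screened on day 3 and diagnosed on day 25, which selects on a consequence of screening.

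**Detail for the full plan.** Date ordering might be left to programming. But the article states an assignment rule, and that rule misclassifies these men if applied as written.

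**Size.** A reader might also infer a bias as large as a modest screening effect. The protocol supplies no incidence, no rate of testing after diagnosis and no death risk by group. The 20% in 2.12 is a power input and is not stated to be annual. The value of *q* is unsupported, and on average only about half the month remains after a diagnosis. The highest figures combine every unfavourable input. This objection stands: the mechanism is established and the size is not.

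**Conclusion.** The gap holds in a limited form. As written, the rules let a small group of known prostate cancer cases enter the screening arm through a test that could not have detected the cancer, and the listed confounders cannot correct for it. The bias runs against screening provided newly diagnosed men are more likely to be tested in the rest of the month than other men are in a whole month, as the range ends above imply.

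On assumed inputs it ranges from negligible (0.003 points) to roughly 0.4–0.5 points. It is probably small for all-cause mortality: the middle case adds 0.025–0.075 points, against the 1.5 points for which 2.12 claims more than 90% power. It could matter more for prostate cancer mortality, where the base risk is low.

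**What to change.** In 2.5 and 2.6, state that a PSA test qualifies as screening only if it is dated before any prostate cancer diagnosis. Ignore tests after diagnosis both for assigning men and for censoring control clones.

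Treat a man diagnosed in the window before any test as compatible with both strategies, and keep both of his clones uncensored for that month. The weight model should then treat him as no longer at risk of artificial censoring from the diagnosis date. Censoring his screening clone at diagnosis would be informative censoring that the listed confounders cannot correct, and it would favour screening. With the inputs of set A, that bias would be at most 0.083% × 22 = 0.018 points: smaller, but avoidable.

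Apply the same rule in the calendar-month analysis (2.11.1) and in any longer window used to assign screening. Section 2.11.2 extends an ascertainment period from 6 to 12 months; if that affects assignment rather than the 6-month filters, more diagnoses will fall inside the window.

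The cost is one date comparison on linked data and a slightly more explicit definition of the screening strategy. The power calculation is unaffected.

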### Screening strategy

2.4

Two types of target-trial emulations are proposed, with both aimed to address the second research question but using different causal inference methods. Two different methods are performed to evaluate whether the results would agree, giving confidence to the conclusions made based on the findings of the study. The first method employs a sequential design and the clone-censor-weight (CCW) approach with enrollment/inclusion based on the attained age (main analysis). The second method performs the analysis based on the calendar year (sensitivity analysis). The CCW approach handles time-varying eligibility and treatment assignment while avoiding the immortal time bias, and the sequential design enables repeated trial emulation at multiple entry points to maximize generalizability and emulate real-world decision-making [20,21].

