#### Statistical considerations

2.10.2

Regarding the CCW trial emulation, two arms will be constructed representing the two screening strategies compared in each pair (screening vs no screening). As the period of eligibility is long (age 75–79 yr), it would artificially inflate the benefit of the no screening strategy as it would contribute to more deaths before the time of censoring in the screening arm. Hence, the trials will be conducted every month during the eligibility period (ie, 75–79 yr of age). Those screened in the control arm will be censored at the first date of their screening during the eligibility 1-mo period, while those not screened in the intervention arm will be censored at the end of the eligibility 1-mo period. Since the datasets will be censored artificially, the inverse probability of censoring weighting (IPCW) will be constructed by applying Cox regression using the list of confounders outlined earlier. Considering that the dataset in the STHLM0 is large (>200 000 men in the age group since 2007) [22], it is computationally prohibitive to construct the censoring weights at each censoring event. We will therefore construct these at the end of the eligibility period. All the datasets will then be appended to perform the analysis and will account for the variance from the same individuals contributing multiple times to the analysis.

Any deviation from the analysis plan or the proposed study design will be described and justified in the study publication.

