#### Analysis based on calendar year

2.11.1

Emulated target trials with observational analog of an intention-to-screen analysis will be conducted, using the CCW method and sequential design every month in alignment to the main analysis. However, the month’s assessment will start from January 1, 2007. Men are ascertained for their screening within the month if they are eligible (75–79 yr). The intervention arm includes eligible men screened with PSA for PCa, while the control arm includes eligible men not screened for PCa during that specific month period. Follow-up starts on January 1, 2007 and ends on December 31, 2023, or when mortality occurs, whichever comes first.

Figure 1B illustrates the flowchart of the inclusion into the trial based on the sensitivity analysis.

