#### Other sensitivity analysis considerations

2.11.2

In addition to the different causal inference methods, this study will consider limiting the recruitment period to December 2018 and December 2013 to allow for longer follow-up time among eligible men. We will consider extending the ascertainment period of the PSA-based screening to 12 mo instead of 6 mo. A deterministic sensitivity analysis for unmeasured confounding using the array method, as described by Schneeweiss [26], will be performed, and the curved surface representing the “fully” adjusted ratio based on the assumed prevalence and varied strength of the unmeasured confounder will be plotted. Moreover, the results will be contrasted with men aged 65–69 and 58–62 yr (in contrast to men aged 75–79 yr).

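### Sections 2.5 and 2.11.1 assign men by their observed PSA test, which contradicts the clone-and-censor rule and, if run, would give screened men a small immortal-time advantage

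*Protocol article*

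**What the plan says.** Section 2.5 sets the window: "Screening is ascertained within the 1st month from trial initiation, representing the eligibility and assignment period". It then allocates by what happened in it: "Eligible men with at least one PSA test in this period will be assigned to the screening arm", and "Those with no PSA test in this window will be assigned to the control arm". Section 2.7 starts the clock at the beginning of the window; of time zero it says that "in the main analysis, this will be the date of age attainment". For the calendar-year analysis, Section 2.11.1 says "the control arm includes eligible men not screened for PCa during that specific month period".

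Other parts of the article describe a different construction. Section 2.4 says "The CCW approach handles time-varying eligibility and treatment assignment while avoiding the immortal time bias". The legend to Figure 1 explains cloning as duplicating each participant, with the copies going to the two strategies. Section 2.10.2 censors control-arm men at their first test in the month, while "those not screened in the intervention arm will be censored at the end of the eligibility 1-mo period".

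Section 2.10.4 adds a stabilized weight for being screened, from a logistic model, and multiplies it by the inverse probability of censoring weight (IPCW). No section says which assignment rule governs.

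**The concern.** Under the Section 2.5 rule each man is in one arm only, and the arm depends on something that happens after time zero. A man who dies on day 10 without a test is a control, even if he would have been tested on day 20. A man counts as screened only if he lived to his test. The screening arm therefore has death-free time built in between time zero and the test. That is immortal time, the bias Section 2.4 says the design avoids. Weighting on baseline confounders does not remove it, because it comes from the assignment rule and not from differences between the men.

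Under cloning, the same day-10 death counts in both arms and the problem does not arise. At stake is whether two analysts following the article would build the same dataset for the prespecified main analysis, and whether one of the two datasets would lean toward screening.

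**Working it through.** **Can both rules be run?** No.

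| Step | Assign by observed test (2.5, 2.11.1) | Clone and censor (Fig. 1, 2.10.2) |
|---|---|---|
| Arms per man at time zero | one | two |
| Control-arm men tested in the window | none, by definition | present, censored at the test |
| Screening-arm men untested in the window | none, by definition | present, censored at window end |
| Untested death in the window | control only | both arms |
| Role for the IPCW | nobody is artificially censored | required |
| Role for a baseline screening weight | required | none evident: the arms hold the same men |

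The 2.10.2 censoring has nobody to act on under the 2.5 rule. The 2.10.4 weight has no imbalance to correct under cloning.

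**The plan's yardstick.** Section 2.12 gives 92.0% power for a 1.5-point reduction (HR 0.956) with 35 000 deaths and 20% screened. Assuming two-sided 5%: √(35 000 × 0.2 × 0.8) × |ln 0.956| − 1.96 = 74.83 × 0.0450 − 1.96 = 1.41, so power is 92.0%. It reproduces. It does not depend on the assignment rule and serves only as a scale; it refers to 17-year mortality.

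**Size of the artefact if the 2.5 rule were run with no true effect.** Let S(t) be survival from time zero, m the 1-month mortality and p the share due to be tested in the window, with test times uniform over it. Let E be the mean of S over the window (the chance of living to the test), about 1 − m/2.

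- Screened risk: 1 − S(t)/E
- Control risk: 1 − S(t)(1 − p)/(1 − pE)
- Difference: S(t)(1 − E)/[E(1 − pE)], approximately S(t) × (m/2)/(1 − p)

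The monthly share tested is not in the article, so p = 2% to 20% is assumed.

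*Input 1: life expectancies in the Introduction* (12.44 yr at age 75, 9.74 yr at age 79). A Gompertz hazard a·exp[b(age − 75)] solved to these gives a = 0.0229 and b = 0.125. Then m = 0.19% at 75 and 0.32% at 79. S(5) is 0.853 and 0.769; S(15) is 0.363 and 0.188. Example at 79 with p = 20%, at 5 years: 0.769 × 0.158%/0.80 = 0.15 points.

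*Input 2: the Section 2.12 assumption* of 0.80 mortality at 17 years. A constant hazard is −ln(0.20)/17 = 0.0947 per year, so m = 0.786%.

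| Spurious difference favouring screening (points) | 1 month | 5 yr | 10 yr | 15 yr |
|---|---|---|---|---|
| Gompertz, age 75 | 0.10–0.12 | 0.08–0.10 | 0.06–0.08 | 0.04 |
| Gompertz, age 79 | 0.16–0.20 | 0.12–0.15 | 0.08–0.09 | 0.03–0.04 |
| Constant hazard 0.0947/yr | 0.40–0.49 | 0.25–0.31 | 0.16–0.19 | 0.10–0.12 |

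The risk ratio inside the first month is 0.45 to 0.50 in every row. On Input 2 the average HR over 17 years is about 0.994 to 0.995.

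**Where the deaths go.** On Input 2 with p = 20%, 786 of 100 000 men die in the month. Of these, 707 are untested and all go to control; about 79 of the 707 would have been tested later that month. A simulation of 10 million men gave first-month death rates of 0.047 (screened) and 0.107 (control) per year under the 2.5 rule, and 0.095 in both arms under cloning.

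**The case against.** The strongest reply is that the article does signal which rule governs. Section 2.4 names clone-censor-weight for the main analysis, the 2.5 heading does so too (with a slip in the abbreviation), Figure 1 defines cloning, and Section 2.10.2 gives the censoring rule for both arms. Section 2.11.1 itself says it uses the same method. On this view the 2.5 sentences only classify the observed data, which any cloned analysis must do to know which copy deviates.

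Most of this stands: cloning is very probably intended, and a reader who infers that the study has chosen a biased design goes further than the text. It does not dispose of the point, because the sentences speak of assignment to an arm, and because the screening weight in 2.10.4 suggests that assignment by observed test may have carried into the analysis.

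The objection that the effect is small also stands for a 1-month window.

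A reader might further infer that the bias becomes large in the sensitivity analysis of Section 2.11.2: "We will consider extending the ascertainment period of the PSA-based screening to 12 mo instead of 6 mo". The text does not support this. The assignment window is 1 month, not 6. The only 6-month intervals in the article are the Section 2.6 rules separating screening from diagnostic tests, so those are the natural object of the extension. No 12-month figure is claimed here.

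**Conclusion.** The contradiction is real and lies in the current text. If the 2.5 rule were run, the direction is fixed (toward screening) and the size is small. At 15 years, the reporting time closest to the 17-year basis of the 1.5-point effect, it is 0.03 to 0.04 points on the life expectancies (2 to 3% of that effect) or 0.10 to 0.12 on the power assumption (6 to 8%). It is concentrated in the first month, so the time-dependent coefficients could show it as an immediate benefit.

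These sizes rest on uniform test timing, 2 to 20% tested per window, and no true effect. For the calendar-year analysis they also assume that each monthly trial starts its clock at the start of the month, as in the main analysis. The constant hazard probably overstates first-month mortality, since risk rises with age.

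The case for correcting the text is that it must define one analysis, more than the size of the bias. The unresolved weight matters for the same reason: if both models use the same confounders over the same month, the product could adjust twice for being tested.

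**What to change.** Replace the assign-by-observed-test sentences in Sections 2.5 and 2.11.1 with text such as:

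> At each time zero every eligible man is cloned to both strategies. A death in the 1-month window before any PSA test counts in both arms. Control clones are censored at a PSA test within the window. Screening clones still untested at the end of the window are censored then. No clone is censored for testing after the window.

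The last sentence is needed. An open-ended rule to censor on deviation would also remove control clones tested years later, and so replace the intention-to-screen contrast of Section 2.9 with a per-protocol one.

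In Section 2.10.4, remove the logistic screening weight for the cloned analysis, or state why it is needed in addition to the IPCW.

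The cost is wording in three sections, plus dropping or justifying one weighting step. No new data are needed, and the Section 2.10.2 censoring already requires the cloned dataset.
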